## Abstract

**Objectives:** Disease-modifying therapies for amyotrophic lateral sclerosis (ALS) are still not satisfactory. The Rho kinase (ROCK) inhibitor fasudil has demonstrated beneficial effects in cell culture and animal models of ALS. For many years, fasudil has been approved in Japan for the treatment of vasospasm in patients with subarachnoid hemorrhage with a favorable safety profile. Here we describe a clinical trial protocol to repurpose fasudil as a disease-modifying therapy for ALS patients.

**Methods:** ROCK-ALS is a multicenter, double-blind, randomized, placebo-controlled phase IIa trial of fasudil in ALS patients (EudraCT: 2017-003676-31, NCT: 03792490). Safety and tolerability are the primary endpoints. Efficacy is a secondary endpoint and will be assessed by the change in ALSFRS-R, ALSAQ-5, slow vital capacity (SVC), ECAS, and the motor unit number index (MUNIX), as well as survival. Efficacy measures will be assessed before (baseline) and immediately after the infusion therapy as well as on days 90 and 180. Patients will receive a daily dose of either 30 or 60 mg fasudil, or placebo in two intravenous applications for a total of 20 days. Regular assessments of safety will be performed throughout the treatment period, and in the follow-up period until day 180. Additionally, we will collect biological fluids to assess target engagement and evaluate potential biomarkers for disease progression. A total of 120 patients with probable or definite ALS (revised El Escorial criteria) and within 6–18 months of the onset of weakness shall be included in 16 centers in Germany, Switzerland and France.

**Results and conclusions:** The ROCK-ALS trial is a phase IIa trial to evaluate the ROCK-inhibitor fasudil in early-stage ALS-patients that started patient recruitment in 2019.

## Background and Preclinical Data

Up to now only riluzole and edaravone have been approved as disease-modifying treatments for amyotrophic lateral sclerosis (ALS), but their efficacy is limited. Thus, there is an urgent need to identify more efficient disease-modifying drugs to improve function and prolong survival for this devastating motoneuron disorder.

Rho kinase (ROCK) has recently emerged as a novel therapeutic target for neurodegenerative disorders [reviewed in (1)]. ROCK is a serine/threonine kinase with two isoforms: while ROCK1 is expressed preferentially in peripheral tissue, ROCK2 is highly expressed in the central nervous system (CNS). Axonal growth inhibitory molecules (e.g., Nogo, MAG, OMgp, ephrins, semaphorins) bind to specific extracellular receptors and signal via ROCK to trigger axonal degeneration, growth cone collapse, and impaired axonal regeneration. In non-neuronal structures, regulation of the actin cytoskeleton plasticity by ROCK also mediates vasoconstriction and vascular remodeling (2). Interestingly, ROCK also regulates cell survival via Akt and mTOR (3–5).

Levels of ROCK increase with age and tissue of ALS patients show increased levels of ROCK2 as well as its downstream targets LIMK1 and cofilin (6, 7). Moreover, in the SOD1 (G93A) mouse model of ALS, increased ROCK activity results in higher levels of phosphorylated adducin as well as activation of phosphatase and tensin homolog (PTEN) and decreased Akt activity, suggesting a deactivation of these cell survival pathways (5). These findings validate the known effects of ROCK activation on pathways regulating the plasticity of the actin cytoskeleton and neuronal survival. Adducin is phosphorylated by ROCK and promotes the interaction between actin and spectrin resulting in actin bundling and stabilization of the cytoskeleton (8). PTEN activation by ROCK is important for its effects on neuronal survival. Since PTEN inhibits phosphatidylinositol (3,4,5) tris-phosphate, which is a central activator of Akt/PKB signaling, PTEN activation by ROCK also exerts negative effects on cell growth, proliferation and metabolism. Via this pathway active ROCK not only to inhibits Akt but also the mammalian target of rapamycin (mTOR) complex 1, which is also an important positive regulator of protein synthesis, cell growth and regeneration (9).

ROCK can be inhibited by fasudil, an isochinoline derivative that was originally developed as a vasodilatory drug and licensed in Japan in 1995 for the treatment of vasospasm following subarachnoid hemorrhage (SAH). Several thousands of patients have been treated with fasudil since. Fasudil has also been tested in numerous clinical trials for other applications, most frequently in cardiovascular disease, such as angina pectoris, Raynaud's syndrome, pulmonary hypertension and arterial hypertension (2). In the CNS, the effects of fasudil were assessed in a phase III trial in patients with acute ischemic stroke, where fasudil treatment significantly improved clinical outcome (10). Significant amounts of fasudil are taken up in the brain (11). Although only intravenous formulations of fasudil are licensed in Japan and China, oral (tablet) formulations, including extended release capsules, were used in clinical trials in humans. The longest published exposure to fasudil in humans is 8 and 12 weeks for angina pectoris and pulmonary arterial hypertension, respectively. Side effects included allergic skin reactions, a slight drop in systolic blood pressure and reversible renal impairment without major safety concerns arguing against longer dosing as required for the treatment of ALS (12, 13). Because of ample clinical experience and a well-known safety profile, fasudil represents an excellent candidate for repurposing as a disease-modifying therapy in ALS. Most importantly, in the SOD1 (G93A) mouse model of ALS, fasudil prolonged survival and improved motor function, which was independently reproduced by two groups (5, 14, 15). Fasudil also improved the regenerative response in the neuromuscular junction, which was accompanied by a modulation of microglial activity. ROCK inhibition not only influenced the morphology of microglia, but also attenuated the lipopolysaccharide-induced release of chemokines and cytokines (14, 16). Other groups showed beneficial effects in the SMN1 knockdown model of spinal muscular atrophy (17). These preclinical data, therefore, suggests ROCK as a novel drugable target with disease-modifying effects in ALS.

## Methods, Design and Analysis

### Objectives

The primary objective of this phase IIa study (proof-of-concept study) is to evaluate the safety and tolerability of intravenous fasudil in two different doses. Participants will be treated for 20 days and followed up for a period of 6 months. Secondary objectives include the survival time and the change of revised ALS Functional Rating Scale (ALSFRS-R), ALS Assessment Questionnaire (ALSAQ-5), Edinburgh Cognitive and Behavioral ALS Screen (ECAS), Motor Unit Number Index (MUNIX) and slow vital capacity (SVC) from baseline to 4 weeks, 3 months, and 6 months after treatment initiation. A further secondary aim is to determine safety and tolerability until the end of the 4 weeks infusion period.

### Study Design

ROCK-ALS is a multi-center, international, randomized, double-blind, placebo-controlled, prospective, dose-finding Phase IIa trial. During its design we considered the “Guideline on clinical investigation of medicinal products for the treatment of amyotrophic lateral sclerosis” of the European Medicines Agency (EMA) where appropriate and the protocol adheres to the “Standard Protocol Items for Randomized Trials” (SPIRIT). It has been registered with the European Clinical Trials Database (Eudra-CT, https://eudract.ema.europa.eu/) under the number 2017-003676-31, with the German Clinical Trials Register (DRKS) under the number DRKS00013948, and on clinicaltrials.gov (NCT03792490). Figure 1 shows the design of the trial.

**Figure 1 F1:**
[figure not shown]
Scheme of trial (drawn to time scale). V, visit; bid, two times daily.

### Participants

#### Inclusion and Exclusion Criteria

Patients with clinical probable, probable laboratory supported or definite ALS and a disease duration of more than 6 and less than 18 months (disease onset defined as date of first muscle weakness, excluding fasciculations and cramps) are eligible for participation in the ROCK-ALS trial. A co-medication with riluzole is compulsory. A previously started treatment with edaravone should be continued throughout the trial. The slow vital capacity must be at least 65% of normal. Main exclusion criteria are previous tracheostomy, continuous assisted ventilation, gastrostomy, severe arterial hypotension, and liver or kidney insufficiency. Importantly, there should be no personal and family history of intracerebral aneurysms or Moyamoya disease due to a theoretical risk of intracranial hemorrhage associated with fasudil treatment. The full list of inclusion and exclusion criteria is depicted in Table 1.

**Table 1 T1:** Inclusion and exclusion criteria.

**Inclusion criteria**	**Exclusion criteria**
•Probable (clinically or laboratory) or definite ALS according to the revised version of the El Escorial World Federation of Neurology criteria •Disease duration more than 6 months and less than 18 months (inclusive). Disease onset defined as date of first muscle weakness, excluding fasciculations and cramps •Vital capacity more than 65% of normal (SVC; best of three measurements) •Age: ≥18 years •Patients have to be treated with Riluzole (2 × 50 mg/d), must be stable for at least 4 weeks before randomization •Patients who have started on Edaravone therapy shall continue Edaravone treatment. Edaravone treatment must not be discontinued for reasons of trial participation. •Women of childbearing age must be non-lactating and surgically sterile or using a highly effective method of birth control and have a negative pregnancy test. Acceptable methods of birth control with a low failure rate i.e., <1% per year) when used consistently and correct are such as implants, injectables, combined oral contraceptives, hormonal intrauterine devices (IUDs), sexual abstinence or vasectomized partner •Capable of thoroughly understanding all information given and giving full informed consent according to GCP •Patients have to have a valid health insurance, when recruited in a center in France	•Previous participation in another clinical study involving trial medication within the preceding 12 weeks or five terminal half times of the longest to be eliminated trial medications (whichever is longer) or previous participation in this trial •Tracheostomy or continuous assisted ventilation of any type during the preceding 3 months before randomization or a significant pulmonary disorder not attributed to ALS, which may complicate the evaluation of respiratory function, intermittent non-invasive ventilation is permitted. •Patients with a history of intracranial bleeding, known intracerebral aneurysms or Moyamoya disease, or positive family history for the above. If only family history positive, MR- or X-ray-based cranial imaging not older than 24 months must confirm absence of bleeding, aneurysms or Moyamoya. •Gastrostomy •Any medical condition known to have an association with motor neuron dysfunction or involving neuromuscular weakness or another neurodegenerative disease, e.g., PD or AD, which might confound or obscure the diagnosis of ALS •Presence of any concomitant life-threatening disease or impairment likely to interfere with functional assessment •Patients with known arterial hypotension (resting blood pressure <90/60 mmHg) or previous hypotensive episodes or requiring treatment for increasing of blood pressure, such as fludrocortisone, midodrine, etilefrine, cafedrine, or theodrenaline •Patients with an uncontrollable or unstable arterial hypertensive disease (resting blood pressure >180 mmHg systolic and/or >120 mmHg diastolic under current antihypertensive medication) •Known pulmonary hypertension and any medication prescribed for treatment of pulmonary hypertension •Confirmed hepatic insufficiency or abnormal liver function (stable ASAT and/or ALAT >3 times the upper limit of the normal range) and determined to be non-transient through repeat testing •Renal insufficiency with a glomerular filtration rate (GFR) <60 ml/min/1.73 m^2^ (calculated by MDRD equation) and determined to be non-transient through repeat testing •Major psychiatric disorder, significant cognitive impairment or clinically evident dementia precluding evaluation of symptoms •Hypersensitivity to any component of the study drug •Liable to be not cooperative or comply with the trial requirements (as assessed by the investigator), or unable to be reached in the case of emergency •Pregnant or breast-feeding females or females with childbearing potential, if no adequate contraceptive measures are used •Prisoners or subjects who are involuntary incarcerated •Patients subject to legal protection measures

#### Recruitment

Patients will be recruited and assessed for eligibility by the ALS outpatient clinics of the highly specialized academic centers taking part in the study, where several hundred ALS patients are seen each year on average. Referring centers and established neurologists will be informed about the ROCK-ALS trial by direct contact and information letters. Patient information sheets and information leaflets for medical professionals (primary care physicians and neurologists) will be issued and distributed to national patient organizations of the participating countries which will be asked to make the information available on their websites. A website for the ROCK-ALS trial has been launched to deliver information for patients and medical professionals (http://rock-als.uni-goettingen.de).

### Randomization, Stratification and Blinding

This trial has three parallel groups: fasudil 15 mg twice daily, fasudil 30 mg twice daily, and matching placebo. Patients are randomized to treatment using an allocation ratio of 1:1:1. The randomization list will be centrally generated using a computerized system stratified by geographical region and type of onset (bulbar, spinal). Patients will be assigned to the bulbar or spinal stratum according to the location of the earliest experienced ALS symptom (defined by the first muscle weakness or in the case of bulbar onset, by the presence of dysarthria and/or dysphagia). In the case of a patient with simultaneous onset of spinal and bulbar symptoms, onset will be defined as bulbar. Cervical and respiratory onsets are stratified to the spinal onset stratum. The randomization list will be generated by the Biometry and Bioinformatics Core using a pseudo-random number generator.

This study includes double-blind (participant- and investigator blind) treatment. Study medication will be packed and blinded by the Pharmacy at University of Leipzig Medical Center, Germany, according to the randomization list. Each patient medication package will be sent together with the sealed unblinding codes to the sites. The investigator at the site will take care that each patient is provided with the study medication box of the correct randomization number. The randomization list will be kept in safe and confidential custody at Pharmacy at University of Leipzig Medical Center, Germany. For all patients, emergency codes will be available to the investigator. A code, which reveals the treatment group for a specific study patient, may be opened during the study only if the choice of treatment depends on the study subject's therapy assignment. During the study, emergency unblinding should occur only by accessing the study patient's emergency code.

### Drug Procurement and Intervention

Fasudil hydrochloride hydrate will be delivered as medicinal product to the Pharmacy at University of Leipzig Medical Center, Germany, and the trial medication as well as the according placebo will be produced, packaged, stored, blinded, labeled, and shipped to the trial sites in accordance with the regulations of the participating country and good manufacturing practice (GMP) (Annex 13 of the EU Guideline for GMP).

Trial medication will be supplied as fasudil hydrochloride hydrate solution 30 mg for IV application (2 × 1 ml of 15 mg/ml fasudil hydrochloride hydrate), or fasudil hydrochloride hydrate solution 15 mg for IV application (1 ml of 15 mg/ml fasudil hydrochloride hydrate and 1 ml NaCl 0.9%). The appropriate Placebo to fasudil hydrochloride solution will be supplied as 2 × 1 ml NaCl 0.9%. Placebo solution is identical in appearance to the study medication (clear, colorless fluid), but does not contain the active ingredient.

The trial drug or placebo has to be diluted in 100 ml NaCl 0.9% prior to administration and is administered two times daily IV as infusion over 45 min using a CE-certified infusion pump. The second application starts 7 ± 1 h after the start of the first application.

### Study Procedures

The trial is structured into 24 visits (V0–V23). V0 is the screening visit and may take place up to 42 days before the first treatment. Treatments are then performed twice daily from V1 to V20 on work days, excluding week-ends and holidays. Subsequently, trial participants are seen at three follow-up visits, V21, V22, and V23, at 45, 90, and 180 days after baseline, respectively. The detailed trial plan is shown in Table 2.

**Table 2 T2:** Trial visits schedule.

**Action visit**	**V0 screening**	**V1 BL**	**V2**	**V3**	**V4**	**V5**	**V6**	**V7**	**V8**	**V9**	**V10**	**V11**	**V12**	**V13**	**V14**	**V15**	**V16**	**V17**	**V18**	**V19**	**V20**	**V21**	**V22**	**V23**
Day (d)		1	2	3	4	5	8	9	10	11	12	15	16	17	18	19	22	23	24	25	26	45	90	180
Permitted delta in days (±) to d1	−42		0	0	+3	+3	+4	+4	+4	+4	+4	+4	+4	+4	+4	+4	+4	+4	+4	+4	+4	±3	±4	±5
		Treatment must be completed within 30 days, with a max. of 3 consecutive non-treatment days																						
Treatment IV 2 times daily		x	x	x	x	x	x	x	x	x	x	x	x	x	x	x	x	x	x	x	x			
Screening assessment																								
Patient information, informed consent	X																							
Inclusion/exclusion criteria	X																							
Demographics	X																							
Medical history	X																							
Diagnosis according to revised EEC	X																							
Physical examination	X																							
Randomization^#^	X^#^																							
Recurrent additional status data																								
Concomitant treatment history	X	X		X				X						X							X	X	X	X
Vital signs (pulse, BP)^**^	X	X	X	X	X	X	X	X	X	X	X	X	X	X	X	X	X	X	X	X	X	X	X	X
Height (only at screening), weight	X																				X		X	X
Endpoint assessment																								
ALSFRS-R		X																			X		X	X
Vital capacity (VC)^***^	X	X																			X		X	X
ALSAQ-5		X																			X		X	X
MUNIX		X^§^																			X		X	X
ECAS		X																			X		X	X
Safety assessment																								
Laboratory tests^^*^^,^^***^^	X	X		X				X						X							X	X	X	X
Pregnancy test^***^	X																							
Adverse events	X^****^	X	X	X	X	X	X	X	X	X	X	X	X	X	X	X	X	X	X	X	X	X	X	X

* *Laboratory tests: RBC, WBC, PLT, creatinine, GFR (MDRD), ALAT, ASAT, GGT, and CK, glucose*.

** *BP and pulse. On V1-V20 to be captured before and at 0, 10, 20, 30, 45, and 60 min after each administration of trial medication*.

*** *If not routine please perform only after informed consent. Pregnancy tests are to be repeated in case of suspicion and/or clinical signs of pregnancy during the course of the study participation*.

**** All Adverse Events must be collected from randomization. X

§ Baseline MUNIX analysis can be performed up to 2 weeks before V1. X

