# *Randomization should be done only after all inclusion and exclusion criteria have been verified*.

### Outcomes

#### Primary Endpoints

Primary endpoints are safety and tolerability. The treatment with fasudil is considered safe for an individual patient if no drug-related serious adverse events (SAE) is recorded through to visit V23. The treatment with fasudil is considered tolerable if participants do not discontinue treatment due to suspected drug-related adverse events (AE). The proportions of patients for whom the treatment is tolerable/safe are derived for each treatment group.

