#### Primary Analysis

The study will yield information about safety, tolerability, and efficacy. The main focus of the primary analysis is to determine whether either one or both doses are safe and tolerable. Each patient will be treated with fasudil or placebo over 45 min twice a day for 20 days. Significant drug intolerance will result in stopping the infusion and termination of the trial participation for this patient.

The proportions of patients for whom the treatment is tolerable/safe are derived for each treatment group. For both active treatment groups and for both, safety and tolerability, separately the difference in proportions to the placebo group will be calculated with its 95% confidence interval. Subsequent analyses will model tolerability and safety in logistic regressions adjusting for randomization stratification factors and important prognostic factors assessed at baseline. Treatment group differences will be reported in terms of odds ratios with 95% confidence intervals.

Primary analyses of safety and tolerability will be carried out on the ITT population. For the purpose of the tolerability analyses, subjects who discontinue during the treatment period will be considered as worst case, i.e., no drug tolerability. If a number of patients withdraw from the study following completion of the treatment period, there observations will be dealt with as independent right censoring and the time to first drug-related SAE will be considered as primary endpoint. The difference in proportions free of any drug-related SAE at V23 will be assessed using Kaplan-Meier estimates and corresponding 95% confidence intervals. Subsequent analyses will model time to first drug-related SAE in Cox proportional hazard regressions adjusting for randomization stratification factors and important prognostic factors assessed at baseline. Treatment group differences will be reported in terms of hazard ratios with 95% confidence intervals. The ITT analyses will be complemented with a per-protocol (PP) analysis. Differences between both analyses will be reported and evaluated in detail.

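### The only scheduled pregnancy test is at V0, up to 42 days before the first infusion, so a symptomless and unsuspected pregnancy detectable only after V0 would not be found before dosing

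*Protocol article*

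**What the plan says.** The Study Procedures section of the protocol article sets the screening window: "V0 is the screening visit and may take place up to 42 days before the first treatment". The permitted-delta row of Table 2 gives the same limit, -42 days under V0.

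In Table 2 the pregnancy-test row has one mark, at V0. The rows for the inclusion and exclusion criteria and for randomization are also marked only in the V0 column. A footnote gives the only rule for repeating the test: "Pregnancy tests are to be repeated in case of suspicion and/or clinical signs of pregnancy during the course of the study participation". Another footnote lists the laboratory panel, which is repeated at V1: "Laboratory tests: RBC, WBC, PLT, creatinine, GFR (MDRD), ALAT, ASAT, GGT, and CK, glucose". A third footnote governs randomization: "Randomization should be done only after all inclusion and exclusion criteria have been verified".

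Table 1 deals with pregnancy twice. A woman of childbearing age who is not surgically sterile must be "using a highly effective method of birth control and have a negative pregnancy test", and the exclusion list contains "Pregnant or breast-feeding females or females with childbearing potential, if no adequate contraceptive measures are used". Acceptable methods are those that fail in under 1% of users per year when used consistently and correctly. Table 1 sets no maximum age for the negative test.

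**The concern.** Pregnancy status can change within six weeks. A site that follows the schedule exactly may give the first infusion on the strength of a 42-day-old result. Nothing else scheduled at V1 would reveal a pregnancy in the meantime: the laboratory panel has no pregnancy marker, and the eligibility check is tied to randomization, not to the first dose.

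Other eligibility measurements are refreshed on the first dosing day. Liver enzymes, GFR and vital capacity, each with a limit in Table 1, are measured at V0 and again at V1. The pregnancy test is not.

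At stake is the avoidable exposure of a woman whom Table 1 means to exclude. Because "Patients are randomized to treatment using an allocation ratio of 1:1:1", two in three such women would receive fasudil. The document gives no reproductive-toxicity data, so the harm per case cannot be quantified from it.

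**Working it through.** **The plan's own figure.** The text and the permitted-delta row of Table 2 agree on a maximum of 42 days from V0 to V1. As the pregnancy test is marked only at V0, 42 days is also the longest time from the last scheduled test to the first infusion. A test at V1 would reduce it to 0.

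**Inputs from the document.** Longest gap 42 days; contraceptive failure limit 1% per year; allocation 1:1:1; treatment completed within 30 days.

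**Assumptions, not in the document.** Number of women of childbearing potential: 10 to 30. A shorter gap for comparison: 14 days. Lag from conception to a positive test: 14 days. Share found on suspicion before V1: one half. Pregnancy rate before V0, when trial contraception was not yet assured: 10% per year.

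**Added cover of a V1 test, per woman.** With a fixed detection lag, a V1 test adds a window of conceptions as long as the V0-V1 gap.
- 42-day gap: 0.01 × 42/365 = 0.00115, or 0.115%. The compound form, 1 − 0.99^(42/365), gives 0.00116.
- 14-day gap: 0.01 × 14/365 = 0.00038, or 0.038%.

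**Expected pregnancies in the trial, 42-day gap.**

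| | 10 women | 30 women |
|---|---|---|
| All arms | 0.0115 | 0.0345 |
| Two fasudil arms (× 2/3) | 0.0077 | 0.0230 |
| All arms, half found on suspicion | 0.0058 | 0.0173 |
| Fasudil arms, half found on suspicion | 0.0038 | 0.0115 |

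**Sensitivity to the period before V0.** With a 14-day lag, the 42 covered days begin 14 days before V0. At 10% per year for those 14 days and 1% for the other 28: 0.10 × 14/365 + 0.01 × 28/365 = 0.00384 + 0.00077 = 0.0046, or 0.46% per woman. That is 0.046 (10 women) to 0.138 (30 women) in all arms, and 0.031 to 0.092 in the fasudil arms.

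**What a V1 test would not cover.** Conceptions in the 14 days before V1 and during up to 30 days of treatment: 0.01 × 44/365 = 0.0012, or 0.12% per woman. At the 1% rate the added test therefore covers 42/(42 + 44) = 49% of the combined window at the longest gap, and 14/(14 + 44) = 24% at a 14-day gap.

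**The case against.** The strongest case against is that the risk is already controlled and the remainder is negligible. Table 1 requires a negative test and highly effective contraception or surgical sterility, and it excludes women without adequate contraception. The repeat-test footnote applies throughout study participation, which reads as including the time between V0 and V1. It also names suspicion separately from clinical signs, so a missed period or a reported contraceptive lapse can prompt a test in a woman without symptoms.

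That last point stands and limits the concern. A reader might infer that every symptomless pregnancy arising in the gap would go undetected before dosing. The document does not support this: a symptomless but suspected pregnancy must be tested. What remains is a pregnancy that raises neither suspicion nor signs.

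The figures also use the longest permitted gap and the contraceptive ceiling, and a V1 test covers at most about half of the combined window at that rate. Both remarks are correct. They keep the point minor but do not remove it. The 1% limit presumes consistent and correct use, so the lower figures are not an upper bound. Partial cover is still worth having when it costs a urine strip at a visit already attended.

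Finally, a condensed article may omit operational detail found in the full protocol. Here, however, Table 2 assigns the test to one visit and a footnote states the repeat rule, so the point concerns what is stated.

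**Conclusion.** The concern holds in a narrow form. Under the schedule as printed, a pregnancy that is both symptomless and unsuspected, and that becomes detectable between V0 and V1, would not be found before the first infusion. This is a low-frequency patient-safety gap worth considering, with about 0.12% per woman at the longest gap and the 1% limit. Even the less favourable sensitivity case stays below 0.14 expected pregnancies in the trial. All trial totals rest on an assumed number of women, and the sensitivity case also on the assumed detection lag and the rate before V0.

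Two stronger inferences are not supported. The plan does not contradict itself: criteria are verified before randomization, as it says, and the weakness is only the timing of one check. Nor does the point touch the primary analysis, the sample size or the error rates. I am confident in the reading of the schedule; the frequency is illustrative.

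**What to change.** In Table 2, mark the pregnancy test at V1 as well, with a footnote such as: urine test before the first infusion, women of childbearing potential only; first infusion only if negative. Keep the existing repeat on suspicion or clinical signs, which remains the only check for conceptions just before V1 or during treatment. No other row changes.

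The cost is one table mark, one footnote line and one urine strip per woman of childbearing potential. There is one small downside. Randomization is marked in the V0 column, so a rare positive V1 test leaves a randomized but untreated patient, and "Primary analyses of safety and tolerability will be carried out on the ITT population", where she would remain. No statistical figure in the plan needs revision.
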